#### (6) Exploratory efficacy assessment

- From the end of the treatment period until the follow-up visit, the following items are investigated:  
whether additional invasive medical procedures related to low back pain were performed [e.g., injection therapy such as nerve block, radiofrequency ablation], whether strong opioid analgesics were used, and whether lumbar surgery was performed.

#### (7) Monitoring of adverse events

- In addition to these assessment visits, adverse events are checked frequently during the treatment period through interviews or questioning whenever necessary.

---

### 5) Early Discontinuation Visit

Participants who have received **at least one session** of the study intervention and then meet the criteria for early termination of the clinical trial will attend an **unscheduled visit 8 weeks after the last treatment session** to undergo an assessment visit. In principle, this assessment should be performed as an in-person visit; however, at the participant's request, items other than physical examination, vital signs, physical function tests, and imaging evaluation may be replaced by **telephone consultation** to the greatest extent possible.

If the clinical trial is terminated early or the participant drops out according to the discontinuation/withdrawal criteria, **no additional follow-up assessments** beyond this early termination visit will be conducted.

---

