#### (2) Rationale for the number of participants in the pilot clinical study

##### ☐ Analysis of previous studies

The sample size for this study was calculated based on the results reported in a previous similar clinical study, using **Cohen's effect size**.

In the previous study, the change in low back pain NRS score in the **Chuna + usual care group** was  $3.02 \pm 1.72$ , whereas in the **usual care group** it was  $1.36 \pm 1.75$  ( $p < 0.001$ ). Based on these data, the effect size (Cohen's  $d$ ) was calculated to be  $d = 0.96$ .

Assuming a two-tailed test, significance level  $\alpha = 0.05$ , and statistical power  $(1 - \beta) = 80\%$ , the following formula was used:

$$n = 2 \times [(Z_{\{\alpha/2\}} + Z_{\beta})^2 / d^2]$$

Here,  $Z_{\{\alpha/2\}}$  is the Z value for a two-sided test at significance level 0.05 (1.96), and  $Z_{\beta}$  is the Z value for 80% power (0.84).

The calculation indicated that the **minimum required sample size per group is 18 participants**.

Taking into account an anticipated **20% dropout rate** during the study, the final target sample size was set at **23 participants per group**, resulting in a total of **46 participants** to be enrolled.

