## 3) Treatment visits (Visits 3–10; both groups)

(1) Chuna + usual care group (Group I; Visits 3–10)

- Starting immediately after the baseline visit, participants receive treatment **twice per week for 4 weeks**, for a total of **8 sessions** according to the allocated intervention (usual care + Chuna).

(2) Usual care-only group (Group II; Visits 3–10)

- Starting immediately after the baseline visit, participants receive **usual care only** twice per week for 4 weeks (8 sessions).

(3) Assessments at each treatment visit (both groups)

- Before treatment at each visit, the following items are checked:
  - Occurrence of adverse events since the previous visit.
  - Vital signs: sitting blood pressure, pulse rate, body temperature (measured after at least 5 minutes in the sitting position without abrupt postural changes).

---

**4) Assessment visits** (same for Groups I and II – Visits 2, 10, and 11)

(1) All participants who pass screening will visit the outpatient clinic at baseline, at the end of the treatment period (4 weeks after baseline), and 8 weeks after completion of all treatments (12 weeks after baseline) to undergo the following assessments.

(2) Vital signs

(3) Assessment of subjective symptoms and function

- Primary and secondary efficacy outcomes are assessed using questionnaires on pain intensity and function: NRS, ODI, EQ-5D-5L, and RMDQ.

(4) Physical examination

- Lumbar range of motion (ROM):  
Flexion, extension, lateral flexion (right and left), rotation (right and left).

(5) Imaging evaluation

- Standardized lumbar spine AP and lateral standing radiographs (L-spine AP & lateral standing view) are obtained.
- Based on the acquired images, vertebral-level relative angles (flexion, extension, lateral bending, rotation) and Chuna malposition diagnosis results are derived using a DICOM labeling program and compared across time points.

(Note: No separate imaging assessment is performed at Visit 2; the imaging evaluation at Visit 2 is replaced by the screening radiographs obtained at Visit 1.)

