#### ○ Early termination of the clinical trial (for a participant)

1. During the clinical trial, if symptoms improve and, based on both the participant's personal request and the judgement of the clinical trial physicians, it is determined that no further treatment is necessary, the clinical trial may be **terminated early** for that participant.
2. Participants whose clinical trial participation is terminated early for this reason are **not** included in the discontinuation/withdrawal group and are considered to have been **fully compliant with treatment**.

---

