## 15. Statistical analysis

The analysis sets used for the evaluation of data obtained in this clinical trial will be defined as follows:

- **Intention-to-treat (ITT) set**
  - The ITT set consists of **all participants who were randomized and received the trial intervention at least once**.
- **Full analysis (FA) set / Full analysis set (FAS)**
  - The FAS consists of all participants who:
    - were randomized, and
    - received the trial intervention at least once, and
    - have **at least one post-baseline efficacy assessment**.
  - The FAS follows the ITT principle and will be used as the **primary analysis set for efficacy**.
- **Per-protocol (PP) set**
  - The PP set includes participants who meet **all** of the following conditions:
    1. Fully satisfy the **inclusion and exclusion criteria**.

2. Have completed at least the **minimum predefined number of treatment sessions** (patients who received **5 or more** of the total 8 planned treatment sessions).
  3. Patients whose treatment was completed because they **met the predefined criteria for treatment completion due to symptom improvement**.
- **Safety analysis (SA) set**
    - The safety analysis set consists of all participants who were randomized and received the trial intervention **at least once**, and for whom **at least one safety assessment** was performed.
    - The SA set will be used for **all safety analyses**.
- 

In this clinical trial, the general principle for statistical analysis is as follows:

- All statistical tests will be **two-sided**, with a **significance level of  $\alpha = 0.05$** .
- Efficacy analyses will primarily be performed using the **full analysis set (FAS)**, with the **PP set** used as a **supplementary analysis**.
- Safety analyses will be performed in the **ITT (SA) set**, i.e., all randomized participants who received at least one treatment.

For missing data:

- For **continuous efficacy variables** in the FAS, missing values will be imputed using the **Last Observation Carried Forward (LOCF)** method, replacing missing values with the most recent available value prior to the missing time point.
- For all other variables, missing data will **not** be imputed, and analyses will be performed using the observed data as they are.

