#### d. Classification of responders and non-responders and post-hoc analysis

- **Responder definition**
  - ▶ Classification of treatment responders and non-responders
    - Using the change in NRS for low back pain from baseline to each evaluation time point, the **minimal clinically important difference (MCID)** is defined as a **decrease of 2 points** on the NRS.
    - Participants who show a decrease of **2 points or more** on the NRS are defined as having achieved MCID and are classified as the **treatment responder group**.
    - Participants with less than a 2-point decrease are classified as the **non-responder group**.
    - In addition, participants whose trial participation is **terminated early due to symptom improvement** because they meet the early termination criteria are also included in the **responder group**.
- **Post-hoc analysis**
  - ▶ Post-hoc analysis based on responder classification
    - Using the above definition of responders and non-responders, appropriate **post-hoc analyses** will be performed by a professional

statistician to investigate differences in outcomes between groups according to response status.

---

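### Participants who stop early because they improved may have no week-4 NRS, and LOCF then enters them in the primary ANCOVA as zero change; the visit rules conflict and must be reconciled

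*Protocol*

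**What the plan says.** **Stopping for improvement.** Protocol Section 9 lets participation end early when symptoms improve and, on the participant's request and the physicians' judgement, "it is determined that no further treatment is necessary". Such a participant is not counted as withdrawn and is treated as fully compliant (Sections 9 and 10).

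**Assessment after an early stop.** Section 8, item 5 provides an "unscheduled visit 8 weeks after the last treatment session". It adds that no additional follow-up assessments "beyond this early termination visit will be conducted". Telephone may replace the parts that need no physical measurement or imaging.

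**Scheduled assessments.** NRS is taken at baseline, week 4 and week 12 (Section 8, item 4; Section 14.1). Section 8, item 4(1) says that all participants who pass screening attend at these times. For the treatment sessions, Section 8, item 3 states: "Before treatment at each visit, the following items are checked". The items listed are adverse events and vital signs; NRS is not among them.

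**Analysis.** The primary analysis is an ANCOVA of the NRS change to week 4, with baseline NRS as covariate, in the FAS (Section 15). The FAS requires randomisation, at least one treatment and at least one post-baseline efficacy assessment. Missing continuous efficacy values are filled by LOCF, "replacing missing values with the most recent available value prior to the missing time point".

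**Responders.** In Section 15, item 2)d, participants who stop for improvement "because they meet the early termination criteria are also included in the" responder group. Section 14.1, item 5 says the same.

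**The concern.** Each rule is workable alone, but together they penalise success. A participant who improves enough to stop has no NRS at the primary time point, stays in the FAS through the late visit, and receives the baseline score as the week-4 score. The same person is a success in the responder analysis. The PP definition also names these participants, so the supplementary analysis is no obvious safeguard.

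At stake is the primary estimate. The protocol expects such stops, because it compares the rate of early termination for improvement between groups as an exploratory outcome. If one arm improves more, more of its participants are likely to stop, and each counts against it as no improvement. A statistical analysis plan could change the imputation rule, but it cannot recover a week-4 NRS that was never collected.

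**Working it through.** **Planning figures.** Inputs from Section 6, item 3: NRS reductions of 3.02 (SD 1.72) and 1.36 (SD 1.75), 80% power, dropout 20%, and "Assuming a two-tailed test" at 0.05.
- Pooled SD = √((1.72² + 1.75²)/2) = 1.735; d = (3.02 − 1.36)/1.735 = 0.957 (stated 0.96).
- n = 2 × (1.96 + 0.84)²/0.96² = 17.01, rounded up to 18; 18/0.80 = 22.5, rounded up to 23 per group, 46 in total.

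These reproduce. The sample size is not in error.

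**When the late visit falls.** With two sessions a week from week 0, session s falls at about week (s − 1)/2, and the visit at week 8 + (s − 1)/2. Stopping after session 1 gives week 8; after session 7, week 11. A last session as late as week 3.5 gives week 11.5. None is week 4.

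**What LOCF inserts.** The late visit comes after week 4, so it cannot be the most recent earlier value. Treatment sessions schedule no NRS. Baseline is the only candidate, so the imputed change is baseline minus baseline = 0.

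**Loss per participant.** One Chuna participant of 23 with a true fall of 4 to 5 points, scored as 0, lowers the arm mean by 4/23 = 0.17 to 5/23 = 0.22 points. Three such participants, with none in control, reduce the expected difference from 1.66 to 1.66 − 12/23 = 1.14 or 1.66 − 15/23 = 1.01.

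**Loss under assumed stop rates.** Let the true change be normal with the planning values. Suppose that those with a fall of at least t points stop with probability p and are then scored 0. Each arm mean falls by p × [μ·P(X ≥ t) + σ·φ((t − μ)/σ)].
- t = 4: the bracket is 3.02 × 0.2844 + 1.72 × 0.3392 = 1.442 for Chuna and 1.36 × 0.0657 + 1.75 × 0.1279 = 0.313 for control, a gap of 1.129. For p = 0.5 the difference is 1.66 − 0.565 = 1.095.
- t = 5: the brackets are 0.731 and 0.106, a gap of 0.625. For p = 0.25 the difference is 1.66 − 0.156 = 1.504.

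Simulation (40,000 trials per row, 23 per arm, two-sample t-test standing in for the ANCOVA because the protocol gives no baseline correlation):

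| Threshold | Share stopping | Stops, Chuna vs control | Difference | Power |
|---|---|---|---|---|
| none | 0 | 0 vs 0 | 1.66 | 0.89 |
| ≥5 points | 25% | 3% vs 0.5% | 1.50 | 0.82 |
| ≥5 points | 50% | 6% vs 1% | 1.35 | 0.75 |
| ≥4 points | 25% | 7% vs 2% | 1.38 | 0.75 |
| ≥4 points | 50% | 14% vs 3% | 1.09 | 0.57 |

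An ANCOVA version with assumed baseline mean 6, SD 1.4 (clipped to 4–10) and baseline–change correlation 0.35 gives 1.10 and 60% for the last row.

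**The case against.** **The week-4 visit may survive.** Section 8, item 4(1) brings all participants who pass screening to clinic at week 4. Item 5 does not expressly cancel that visit, and its 8-week interval mirrors the regular final follow-up, so it could be read as moving only that last visit. This stands: a missing week-4 NRS follows from one reading of two conflicting rules. Item 5 is, however, the specific rule for early stoppers, and a site that follows it will collect no week-4 value.

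**Withdrawn participants.** A reader might infer that everyone withdrawn under Section 9 is also scored as zero change. The protocol does not support that. It is unclear whether they receive the late visit. Those with no post-baseline efficacy assessment leave the FAS and are not imputed. Someone withdrawn after week 4 already has the value. They may lack a week-4 NRS, but not necessarily with the same result.

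**Best responders.** Section 9 sets no NRS threshold for stopping, so it is an assumption that the stoppers are those with the largest falls. Modest improvers could stop in either arm. A lower threshold does not make the problem milder at a given stopping share, though: at 3 points and 25% stopping (13% vs 4%), the difference is 1.28 and power 0.67.

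**Size and direction.** No stop rate is given, and the mildest tabulated case keeps power above the planned 80%. If Chuna has more such stops, the bias is toward zero, so the risk is a missed effect and not a false claim of benefit. The study is also described as a pilot with an exploratory aim. All this limits how firmly the size can be stated, but it does not remove the fault.

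**The responder rule.** It is explicit and does not feed the primary ANCOVA, so changing it is a separate, secondary matter.

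**Conclusion.** The concern holds in this form: Section 8, items 4 and 5 conflict on whether an improvement-related early stopper has a week-4 assessment. If item 5 is followed, LOCF enters zero change in the primary analysis for people the protocol elsewhere calls fully compliant and responders. The bias runs against whichever arm has more such stops, probably Chuna.

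The size is conditional. If 25% to 50% of those improving by at least 4 or 5 points stop early, the expected difference falls from 1.66 to between 1.50 and 1.09 points, and power from about 89% to between 82% and 57%. This rests on the planning means and SDs, normal changes, and assumed thresholds and stop shares, none of which the protocol supplies for early stops. The zero itself needs no such assumption; it follows from the visit and imputation rules. It should be corrected while the week-4 data can still be collected.

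**What to change.** - **Visits.** Reconcile Section 8, items 4 and 5. Keep the week-4 and week-12 questionnaires (NRS, ODI, RMDQ, EQ-5D), counted from baseline, for every randomised participant who still consents, whether or not treatment has stopped. Telephone is already allowed. Limit this to questionnaires so that it adds no radiographs.
- **Analysis.** In Section 15, use the observed week-4 NRS in the primary ANCOVA and do not carry baseline forward for improvement-related stops.
- **Withdrawals.** State whether participants withdrawn under Section 9 receive the late visit.
- **Responders (secondary).** Classify responders from the observed NRS at each time point, or at least report that version beside the automatic rule in Section 14.1, item 5 and Section 15, item 2)d. The automatic rule rests on a decision by an unblinded participant and physician, and it ignores any later NRS.

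The cost is amendment wording and one extra questionnaire contact for the few who stop early. No additional participants are needed, and the rules for stopping treatment are unchanged.

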## 9. Criteria for discontinuation/withdrawal and early termination of the clinical trial

### ○ Criteria for discontinuation/withdrawal

1. The following medications, which are expected to affect the evaluation of the effectiveness of the interventions, **must not be taken from screening until completion of the clinical trial**.

① Strong opioid analgesics; local anesthetics and corticosteroid preparations administered separately from the trial interventions by the attending physician.

- However, based on the clinical judgement of the investigator, non-steroidal anti-inflammatory drugs and muscle relaxants that are prescribed as needed may be used (see 11. Rescue medication).

② Any other drugs that, in the judgement of the clinical trial investigator, may pose a risk to the participant or introduce bias into the evaluation of the study results.

2. Cases in which the participant requests discontinuation of the trial intervention during the clinical trial, or withdraws consent to participate in the study.
3. Cases in which a serious adverse event occurs and the investigator judges that continuation of the trial is not possible.
4. Cases in which major protocol violations such as violation of inclusion/exclusion criteria are newly identified during the clinical trial.
5. Cases in which, although the early termination criteria are not met, the participant does **not attend at least 5 out of the planned 8 treatment sessions**.
6. Any other cases in which it is considered difficult for the participant to continue in the clinical trial, and the principal investigator/sub-investigator judges that the trial should be discontinued for that participant.

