### 5.2.2 Chuna manual therapy (applied only in the Chuna treatment group)

#### (1) Application of Chuna therapy according to radiograph–based diagnostic results

- In the Chuna treatment group, Chuna manual therapy is performed based on the Chuna diagnostic results derived from the plain radiographs.
- Treatment is provided twice per week for 4 weeks (approximately 15 minutes per session), for a total of 8 sessions.
- According to the diagnostic results, the standardized operating procedures (SOPs) specified in the protocol are used to select the treatment method.
- Based on the classification of Chuna diagnostic results into simple and complex malposition patterns, Chuna treatment methods specified in the SOP are applied to the corresponding vertebral levels.
- When more than one corrective technique is presented in the SOP for a given malposition, the practitioner may choose the most appropriate technique according to clinical judgement.
- If, in the clinical judgement of the practitioner, additional Chuna therapy is required for regions other than the lumbar spine (for example, the pelvis), such techniques may be applied, and these procedures will be recorded in the case report form.
- However, for the lumbar spine itself, no Chuna techniques other than those specified in the SOP may be applied.

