#### (2) Determination of the exact treatment level using ultrasound prior to Chuna therapy

- To ensure accurate contact at the treatment level corresponding to the malposition identified on plain radiographs, ultrasound imaging is used to confirm the vertebral level before Chuna therapy.
- Using a longitudinal view, the shape of the spinous processes is visualized, and the levels are identified sequentially from S1 upwards.
- Once the target level is confirmed, the skin overlying the planned treatment site is marked.
- Chuna techniques are then performed at the marked level, following the standardized procedures described in the SOP.

[figure not shown][figure not shown]

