### 2) Exclusion criteria (Exclusion Criteria)

- ① Patients diagnosed with serious specific diseases that can be the cause of low back pain (e.g., spinal metastasis of tumors, acute fracture and spinal dislocation, scoliosis of moderate or greater severity).
- ② Patients with structural abnormalities of the lumbar spine (sacralization, lumbarization), those with a prior history of osteoporosis, or those in whom fracture of the lumbar spine is suspected.
- ③ Patients who are within 3 months after lumbar spine surgery.
- ④ Patients with other chronic diseases that may interfere with the treatment effect or with interpretation of the study results (e.g., chronic renal failure), as judged by the investigator.
- ⑤ Patients with progressive neurological deficits or serious neurological symptoms such as cauda equina syndrome.
- ⑥ Patients who have internal fixation or stabilizing devices in the lumbar spine due to previous lumbar surgery.
- ⑦ Patients with contraindications to interferential current therapy (ICT), such as cancer-related pain or an implanted pacemaker.

- ⑧ Patients who are currently taking systemic steroids, immunosuppressants, psychiatric medications, or other drugs that may affect the study results, as judged by the investigator.
- ⑨ Patients who have received Chuna therapy within the past week, or who have received strong opioid analgesics, anesthetic agents, or invasive treatments such as acupuncture or injection therapy during that period.
- ⑩ Patients who have received nerve block procedures to the lumbar region within the past 2 months.
- ⑪ Patients who are pregnant, breastfeeding, or planning pregnancy during the study period.
- ⑫ Patients who are scheduled, during the 4-week treatment period, to undergo surgery, procedures, or pharmacologic treatment that may affect evaluation of the study results, without this being under the direction of the study physician.
- ⑬ Any other individuals whom the investigator judges to be inappropriate for participation in the clinical trial.
- 

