## 3) Outline of treatments in each group (summary)

- **Usual care (both groups)**
  - Interferential Current Therapy (ICT) applied to the painful lumbar region for **15 minutes per session**,
  - **Exercise guidance** (pelvic tilt, trunk rotation without weight bearing, knee-to-chest, partial curl-ups, etc.) for about **15 minutes** at each visit,
  - **Lifestyle education** and patient education materials on postures that help prevent low back pain and appropriate working postures.

→ Provided **twice per week for 4 weeks (total 8 sessions)** in both groups.
- **Chuna manual therapy (Group I only)**
  - In addition to usual care, standardized Chuna manual therapy is applied according to the **radiograph-based Chuna malposition diagnosis** confirmed at screening.
  - Techniques are selected according to the SOP for each malposition pattern (simple malposition, specialized techniques for simple malposition, simple techniques for complex malposition, specialized techniques for complex malposition).
  - Chuna therapy is provided **twice per week for 4 weeks (total 8 sessions, about 15 minutes per session)**.
  - Whenever necessary, ultrasound is used before treatment to confirm the exact vertebral level and mark the skin contact point.

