#### (5) Confirmation of inclusion/exclusion criteria

- Final judgement of inclusion and exclusion criteria will be made by reviewing NRS scores, existing medical history, and prior treatment history.

---

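### A late-found eligibility violation ends scheduled follow-up, so the week-4 primary NRS can be lost, possibly more often in the Chuna arm

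*Protocol*

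**What the plan says.** - **Withdrawal.** Section 9, discontinuation/withdrawal item 4, covers "Cases in which major protocol violations such as violation of inclusion/exclusion criteria are newly identified during the clinical trial". It sets no time limit and does not say who judges the violation or on what evidence.
- **Follow-up after withdrawal.** Section 8, 5) gives a participant who has had at least one session a single visit 8 weeks after the last session. It rules out further assessments, including for those who leave under the withdrawal criteria.
- **Primary analysis.** Section 15, 2) a compares the NRS change from baseline to week 4 by ANCOVA.
- **Analysis sets and missing data.** In Section 15 the FAS is the primary efficacy set. It requires randomisation, at least one treatment and at least one post-baseline efficacy assessment; eligibility is not a condition. Missing continuous efficacy values in the FAS are filled by LOCF. Only the supplementary PP set requires full eligibility.
- **Blinding.** Section 7, 2) says that clinical investigators and participants are not blinded; only outcome assessors are.
- **Examination during treatment.** Only Group I receives Chuna: "Treatment is provided twice per week for 4 weeks (approximately 15 minutes per session), for a total of 8 sessions". Section 5.2.2 (2) says that "ultrasound imaging is used to confirm the vertebral level before Chuna therapy", and that "the levels are identified sequentially from S1 upwards". The summary in Section 7, 3) is weaker: "Whenever necessary, ultrasound is used before treatment to confirm the exact vertebral level". Group II receives ICT, exercise guidance and education.
- **Assessment visits.** These are the "same for Groups I and II – Visits 2, 10, and 11", with the same films in both arms.

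**The concern.** Deciding that someone should not have been randomised is one matter; ceasing to measure that person's outcome is another. The protocol joins the two. A participant withdrawn for ineligibility in weeks 1 to 4 loses the measurement on which the primary comparison depends. The value that replaces it is either a baseline score, recorded as no improvement, or nothing at all.

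If this happened equally in both arms and without regard to outcome, the harm would be limited. The text does not secure that. The people who identify violations know the allocation, and one arm has closer contact with the lumbar spine during treatment. Exclusion criterion 2 names sacralization and lumbarization, which are features that could plausibly come to notice when levels are counted from S1. With 23 per arm, a few one-sided cases would be visible in the estimate.

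**Working it through.** **Planning figures (Section 6, 3) (2)).** NRS change is 3.02 (SD 1.72) with Chuna plus usual care and 1.36 (SD 1.75) with usual care.
- Difference: 3.02 − 1.36 = 1.66. Pooled SD: √((1.72² + 1.75²)/2) = 1.735. d = 1.66/1.735 = 0.957, which the plan gives as 0.96.
- n = 2 × (1.96 + 0.84)²/0.96² = 17.01, rounded up to 18. With 20% dropout, 18/0.8 = 22.5, rounded up to 23. The plan's figures reproduce and are not disputed.

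**Timing of the only remaining visit.** Treatment starts immediately after baseline and runs 4 weeks. A last session at week 0 puts the visit at week 0 + 8 = 8; a last session at week 4 puts it at week 4 + 8 = 12. It never falls at week 4. For someone withdrawn before the week-4 assessment, the most recent value before week 4 is baseline, because NRS is not scheduled between the two. LOCF therefore gives a change of 0. If the late visit is also missed, there is no post-baseline assessment and the FAS condition fails.

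**Size, as an illustration.** The protocol gives no rate, so suppose k of the 23 in Group I are withdrawn before week 4 and none in Group II. Had everyone been measured, the difference would be 1.66. These are simple differences in means, without covariate adjustment.
- A, baseline carried forward: 3.02 × (23 − k)/23 − 1.36.
- B, left out of the analysis, would have changed by 0: 3.02 × 23/(23 − k) − 1.36.
- C, left out of the analysis, would have changed by 1.36: (3.02 × 23 − 1.36k)/(23 − k) − 1.36.

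| k | share of Group I | A | B | C |
|---|---|---|---|---|
| 0 | 0% | 1.66 | 1.66 | 1.66 |
| 1 | 4.3% | 1.53 | 1.80 | 1.74 |
| 2 | 8.7% | 1.40 | 1.95 | 1.82 |
| 3 | 13.0% | 1.27 | 2.11 | 1.91 |
| 4 | 17.4% | 1.13 | 2.30 | 2.01 |

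**Power.** By normal approximation, Φ(1.66/(1.735 × √(1/(23 − k) + 1/23)) − 1.96) is 0.90 at k = 0 and 0.87 at k = 4. Loss of precision is minor. The issue is a shift in the estimate whose direction depends on which missing-data route applies.

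**The case against.** A reader might infer that only the Chuna arm is examined level by level, that eligibility is re-judged after randomisation, and that ineligible participants will therefore be found and removed unequally. The documents do not support that reading.

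- Both arms have repeat films with vertebral-level angles at weeks 4 and 12 (Section 8, 4) and Section 14.1), and Section 14.2 calls for physical examination at every visit after randomisation.
- No re-check of eligibility is scheduled. Item 4 acts only on what comes to light.
- Section 8, 1) (5) says the final eligibility judgement "will be made by reviewing NRS scores, existing medical history, and prior treatment history", which omits the films. But the opening of Section 8, 1) excludes anyone with clinically significant abnormalities on the screening assessments, and those include the radiographs. The structural criteria can be seen before allocation.
- The ultrasound serves to locate the treatment level, and the two sections differ on whether it is routine. Most criteria, such as age, NRS, surgery, medication and pregnancy, do not depend on it.
- The FAS has no eligibility condition, so withdrawal does not in itself remove anyone from the primary analysis.

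All of this stands, and it reduces unequal detection to a possibility. It does not remove the follow-up problem. A violation seen on the week-4 film is found at the same visit as the week-4 NRS and need not cost that value, so the shared films do not offset what may be found earlier. The treatment-visit checks in Section 8, 3) list only adverse events and vital signs, and a general physical examination is not level-counting. It is also true that loss of follow-up affects withdrawals for other reasons and in both arms; that widens the case for the fix.

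**Conclusion.** The point holds as a defect in follow-up after withdrawal. Item 4 of Section 9 together with Section 8, 5) allows the week-4 primary outcome of a randomised, treated participant to be lost because of a late-found eligibility violation, and Section 15 then fills it from baseline or drops the participant from the FAS.

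That such losses would differ by arm is a risk, not something the protocol states. It rests on unblinded decisions and on the ultrasound and manual contact confined to Group I before week 4. Its frequency is unknown. If one or two cases arose in Group I only, the planning difference of 1.66 would move to between 1.40 and 1.95 across the scenarios shown; power would hardly change. The stronger conclusion, that ineligible participants are in fact removed unequally, should not be drawn. The change is worth making because it is cheap and protects the primary comparison whether or not the imbalance occurs.

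**What to change.** In Section 8, 5) and Section 9, item 4, state that an eligibility violation found after randomisation does not end the scheduled week-4 and week-12 outcome assessments, and that the participant stays in the FAS in the arm as randomised. Say separately that continuing or stopping the intervention is a clinical decision; no rule for it is proposed here.

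As a minor addition, judge the eligibility condition of the PP set only on data from before randomisation, by someone unaware of the arm, with the same check for all 46 participants. The PP analysis is supplementary and this detail could sit in the SAP. The ultrasound statements in Section 5.2.2 (2) and Section 7, 3) must be reconciled, so that the difference in examination between arms is known.

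The cost is protocol wording and assessment visits already in the schedule. The downside is that a few ineligible participants contribute to the primary analysis, which the ITT principle cited for the FAS in Section 15 already implies.
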